## Abstract

**Background:**

The use of transcatheter aortic valve implantation (TAVI) for treating aortic stenosis (AS) has increased exponentially in recent years. Despite the availability of clinical practice guidelines for the management of valvular heart disease, disparities in quality of care (QoC) for TAVI patients remain widespread across Europe. Tailored QoC measures will help to reduce resource utilization and improve patient outcomes without compromising patient safety. Using a clear set of QoC measures, the BENCHMARK registry aims to document the progress that can be achieved if such tailored QoC measures are implemented.

**Methods:**

The BENCHMARK registry (BENCHMARK) is a non‐interventional, multicenter registry in patients with severe symptomatic AS undergoing TAVI with a 1‐ and 12‐months follow‐up. BENCHMARK will be conducted at 30 centers across Europe and will enroll a total of 2400 consecutive TAVI patients. Patients suffering from severe symptomatic AS who undergo TAVI with a balloon‐expandable transcatheter aortic valve will be included. The registry will comprise four phases: (1) a retrospective baseline evaluation phase; (2) an education phase; (3) an implementation phase; and (4) a prospective effect documentation phase (prospective phase). The registry's primary objectives are to reduce the length of hospital stay and accelerate the post‐procedural patient recovery pathway, but without compromising safety. The study started in April 2021 and has an estimated completion date of May 2023.

**Discussion:**

BENCHMARK will establish QoC measures to reduce resource utilization, intensive care unit bed occupancy, and overall length of hospitalization with uncompromised patient safety post‐TAVI (ClinicalTrials.gov Identifier: NCT04579445).

## INTRODUCTION

1

Transcatheter aortic valve implantation (TAVI) has emerged as standard of care for patients suffering from severe, symptomatic aortic stenosis (AS), irrespective of the level of surgical risk.^1^, ^2^, ^3^, ^4^, ^5^ Since its introduction almost two decades ago,^6^ an evolving understanding of patient and prosthesis selection, increased peri‐procedural expertise, and advances in valve technology have contributed to improved outcomes and patient access to TAVI.^7^

As a consequence of TAVI indications expanding to younger and lower‐risk patients, there has been a clear shift in interest toward reducing healthcare resource utilization, and identifying factors likely to predict potential futility of the procedure^5^, ^8^, ^9^, ^10^ For example, a minimalist approach to help reduce procedure waiting times, resource use and costs, length of hospital stay, and staff workload.^11^, ^12^ Local programs that incorporate procedural algorithms to simplify the TAVI care pathway have been developed by many centers.^8^, ^12^, ^13^, ^14^, ^15^ However, the quality of care (QoC) for TAVI patients across Europe remains highly variable, particularly in terms of effective screening and patient discharge/follow‐up management.^16^, ^17^ A unified strategy is warranted to ensure that all patients receive consistent pre‐, peri‐ and post‐TAVI care and optimized outcomes.^18^

To achieve standardized QoC, some centers of excellence have introduced a dedicated coordinator or TAVI nurse to ensure a streamlined care pathway for all patients.^19^, ^20^ The TAVI coordinator/nurse helps to manage the procedural program for individual patients while maintaining seamless communication with the Heart Team throughout the patient care journey, making the process more streamlined.^19^ One of the TAVI coordinator's roles is to ensure that all relevant screening results (e.g., echocardiography, computed tomography [CT] imaging scans, coronary angiogram, blood tests, etc.) are distributed to all members of the Heart Team promptly to inform patient discussion and to prevent delays in Heart Team recommendations.^5^ Lauck et al.^19^ endorse this coordinated, streamlined approach to reduce the length of hospital stays and appropriately distribute healthcare resources. The recent multicenter European Feasibility and Safety of Early Discharge After Transfemoral TAVI (FAST‐TAVI)^21^, ^22^ and Vancouver 3M (multidisciplinary, multimodality, but minimalist) transfemoral transcatheter aortic valve replacement (TAVR) studies^17^, ^23^, ^24^, ^25^ have shown that adhering to a minimalist strategy, with optimized criteria for risk assessment and patient discharge management, results in a more efficient care pathway, thus reducing the length of hospital stay and enabling a safe and timely discharge for patients. Furthermore, these studies have gained added importance recently due to the unprecedented stress on healthcare resources caused by the Coronavirus disease (Covid‐19) pandemic.^19^, ^26^

A consistent pre‐, peri‐, and post‐procedural management strategy is essential to improve QoC for TAVI patients. Implementing a tailored set of QoC measures as a benchmark for best practice will further reduce resource utilization, intensive care unit (ICU) bed occupancy, and overall length of hospitalization without compromising patient safety post‐TAVI. The BENCHMARK registry aims to document the progress that can be achieved in clinical practice if consistent QoC measures are initiated in TAVI centers and the rationale for this study is supported by the FAST TAVI, the French FAST TAVI 1 and Vancouver 3M TAVR studies.^13^, ^14^, ^17^, ^21^, ^22^

## METHODS/DESIGN

2

The BENCHMARK registry (ClinicalTrials.gov Identifier: NCT04579445) is a non‐interventional, multicenter, international registry that will enroll patients with severe symptomatic AS undergoing transfemoral (TF) TAVI at 30 centers across Europe (Austria, Czech Republic, France, Germany, Italy, Romania, Spain). Each participating center should have a TAVI coordinator in place. The registry will be conducted according to the European Medical Device Regulations and International Organization for Standardization (ISO 14155:2020) and the ethical principles originating from the Declaration of Helsinki. All participants will provide written informed consent before enrolling in the registry. The protocol and patient informed consent forms will be approved by the local Institutional Review Board (IRB)/Independent Ethics Committee (IEC) at each center prior to initiation of the registry.

### Study design

2.1

The BENCHMARK registry will document the effect of introducing tailored BENCHMARK QoC measures (Table 1) into TAVI centers using four distinct phases: Retrospective baseline evaluation phase, education phase, implementation phase, and prospective effect documentation phase (Figure 1). For the baseline evaluation phase (retrospective phase), each center will retrospectively document 30 consecutive patients (*N* = 900) undergoing transfemoral TAVI with a balloon expandable transcatheter aortic valve before introducing the BENCHMARK QoC measures. The TAVI procedure and patient discharge within this phase must have been performed prior to the first educational phone call. For each patient, follow‐up data after 1 and 12 months will be recorded. In the education phase, each center will identify a defined leadership team (i.e., multidisciplinary heart team) to undergo online education on the BENCHMARK QoC measures and best practices. A detailed description of the education phase is shown in Figure 2. During the Implementation Phase, consisting of a 2‐month time window, each center will introduce the tailored QoC measures into their hospital routine. Follow‐up calls will be arranged between the BENCHMARK education team and each center every 2 weeks to offer assistance with regard to implementation progress. Finally, each center will prospectively enroll 50 consecutive patients (*N* = 1500) undergoing TAVI after completing the education and implementation phases. This prospective phase is estimated to be 20 months duration overall, with up to 8 months for patient recruitment and 12 months follow‐up for the last patient included.

**TABLE 1 clc23711-tbl-0001:** BENCHMARK QoC measures

BENCHMARK QoC measures	Implementation description
1. Education of patient and family	The patient, and if the patient is not independent, at least one family member or carer is involved in the patient‐education, and discharge provision is discussed with them prior to the procedure.
2. Education and alignment of the internal team (medical and paramedical)	At least one joint meeting per year is organized to educate all staff involved in the diagnostics, post‐procedural care and intervention of patients with severe AS.
3. Determination of an anticipated discharge date at admission based on pre‐procedural risk stratification and scheduling of post‐procedural diagnostics accordingly	Anticipated discharge date is determined at admission, and post‐procedural diagnostics are scheduled accordingly.
4. Echo‐ or angiographic check at the end of procedure is performed to confirm proper closing of access site and proper management of all complications is done immediately	Echo‐ or angiographic check is performed in the hybrid room, and even minor vascular complications are treated immediately.
5. Early mobilization of the patient	Mobilization of the patient with the help of a nurse is done 4–6 h after the intervention in absence of complications.
6. Using a decision tree to determine the need for new pacemaker implantation without increasing hospital stay	Detailed decision tree with required diagnostic work‐up is in place and has been followed for each patient.
7. Daily visit to patient by implanter and interaction with rest of the team	At least one daily visit of the patient is being done by a TAVI implanter (team) during hospitalization from the day before the intervention up to patient discharge.
8. Criteria based discharge	Early discharge decision protocol (or checklist) is in place and is followed for each patient.

*Note*: The 8 BENCHMARK QoC measures are rated 0%–100%.

Abbreviations: AS, aortic stenosis; Echo, echocardiogram; PPM, permanent pacemaker implantation; QoC, quality of care.

**FIGURE 1 clc23711-fig-0001:**
[figure not shown]
Registry design (retrospective baseline evaluation phase, education phase, implementation phase and prospective effect documentation phase). The registry comprises four phases: (1) A retrospective baseline evaluation phase—this phase is the current status quo and includes documentation of treatment pathways and endpoints of “routine” patients. (2) An education phase, which phase provides education on the BENCHMARK quality of care measures and involves the self‐assessment of centers. (3) An implementation phase, which aims to improve routine hospital quality of care measures. (4) A prospective effect documentation phase—this phase documents the impact of implemented BENCHMARK quality of care measures on treatment pathways, outcomes, safety, and resource utilization. Note, each participating center should have a non‐physician TAVI coordinator in place. QoC, quality of care; TAVI, transcatheter aortic valve implantation

**FIGURE 2 clc23711-fig-0002:**
[figure not shown]
Education pathway (BENCHMARK QoC measures). Pathway stages 1–4: (1) center self‐assessment is performed prior to the online education seminar; (2) online center education on BENCHMARK QoC measures will be arranged by the education team (including the local steering committee member and/or the PI team and the registry management team). A minimum of 3 TAVI Team members, having been identified as a leadership team (TAVI coordinator and further staff members per site), will attend the seminar; (3) a post‐QoC education call to discuss the self‐assessment results and write a final action plan with the leadership team will be arranged 1 week after the education seminar; and (4) a follow‐up call will be arranged to review center progress on BENCHMARK QoC implementation. PI, principal investigator; QoC, quality of care

### Patients

2.2

A total number of 2400 patients aged ≥18 years old with symptomatic AS who undergo TF TAVI with a balloon‐expandable transcatheter aortic valve will be included. Approximately 900 consecutive patients will be documented in the retrospective baseline evaluation phase (30 per center) and 1500 patients in the prospective phase (50 per center). The sample size estimate is based on the ability to discriminate any changes in outcomes between the retrospective baseline evaluation phase and the prospective effect documentation phase.

All patients irrespective of transcatheter valve type or access route, will be documented in an electronic case report form (eCRF) based patient logbook. A defined core data set will be collected for all patients (mortality, stroke, time of discharge/length of hospital stay, readmission).

### Inclusion and exclusion criteria

2.3

In the baseline evaluation phase, inclusion criteria included patients of at least 18 years of age, consecutive patients with severe symptomatic AS who underwent transfemoral TAVI with a balloon‐expandable transcatheter aortic valve prior to the center education on BENCHMARK QoC measures, and if the patient was scheduled to undergo 30‐day and 12‐month follow‐up visits. Patients were excluded from the Baseline Evaluation Phase if their data was incomplete respect to the aims of the registry (length of hospital stay, time on the ICU), they did not provide informed consent, or were pregnant (Table 2).

**TABLE 2 clc23711-tbl-0002:** BENCHMARK inclusion/exclusion criteria

Inclusion criteria	Exclusion criteria
*Baseline evaluation phase*	
Patient is at least 18 years old Consecutive patients with severe symptomatic AS who underwent transfemoral TAVI with a balloon‐expandable transcatheter aortic valve *prior* to the center education on BENCHMARK Quality of Care measures (prior to the pre‐Quality of Care education call) Patient is or was scheduled to undergo 30 days and 12 months follow‐up visits (30 days and 12 month follow‐up: hospital visit or phone call)	Patients with largely incomplete data with respect to the aims of the project. Patients without signed informed consent/data protection statement (unless otherwise agreed by the local Institutional Review Board/Independent Ethics Committee) Pregnancy at time of the TAVI
*Prospective effect documentation phase*	
Patient is at least 18 years old Consecutive patients with a diagnosis of severe symptomatic AS admitted for transfemoral TAVI with a balloon‐expandable transcatheter aortic valve *after* center education on the BENCHMARK Quality of Care measures/*after* the center has passed the Implementation Phase. Patient is scheduled to attend follow‐up visits at the center 30 days and 12 months after the procedure (both visits taking place in the hospital)	Patients without signed informed consent/data protection statement (according to requirements of local Institutional Review Board/Independent Ethics Committee) Pregnancy at time of the TAVI

Abbreviations: AS, aortic stenosis; TAVI, transcatheter aortic valve implantation.

In the Prospective Effect Documentation Phase, the inclusion criteria were patients of at least 18 years of age, consecutive patients with a diagnosis of severe symptomatic AS admitted for transfemoral TAVI with a balloon‐expandable transcatheter aortic valve after center education on BENCHMARK QoC measures/after the center had passed the Implementation Phase, and the patient is scheduled to attend follow‐up visits at the center 30 days and 12 months after the procedure. Patients were excluded from the Prospective Effect Documentation Phase if they did not provide informed consent or were pregnant (Table 2
**)**.

Patients undergoing valve‐in‐valve procedures or repeat TAVI will not be included in the registry.

### Data collection

2.4

Clinical outcome data collected will be based on the center's standard of care for TAVI. Data will be collected according to the timetable set out in Table 3, and include physical assessments, medical history and symptoms, diagnostics, electrocardiography (ECG), echocardiography (Echo), hospitalization and procedural duration, safety parameters, QoL measures, satisfaction surveys, as well as resource utilization parameters. Data will be captured in an eCRF by either a study nurse or physician, and the registry sponsor will check all data for plausibility and completeness.

**TABLE 3 clc23711-tbl-0003:** Data collection schedule

	Baseline evaluation phase (retrospective documentation phase)					Effect documentation of BENCHMARK QoC measures (prospective enrollment phase)				
	Screening/baseline	TAVI	Discharge	30 days visit *Visit or call* (±1 week)	12 months visit *Visit or call* (±3 weeks)	Screening/baseline	TAVI	Discharge	30 days visit (±1 week)	12 months visit (±3 weeks)
Signed informed consent	X^a^					X^b^				
Inclusion/exclusion criteria	X					X				
Referral management	X					X				
Treatment decision	X					X				
Tasks, being impacted by the coordinator								X		
Demographics	X					X				
ECG and Echo	X	X	X	X^c^	X^c^	X	X	X	X	X
Comorbidities	X					X				
Symptoms and social characteristics	X					X				
Risk score (Euro Score II)	X					X				
Frailty, mental, social status	X					X				
Quality of life (TASQ)						X		X	X	X
Procedural details (device success)		X					X			
Length of hospital stay			X					X		
Safety and efficacy variables (VARC‐2)^27^			X	X	X			X	X	X
Rehospitalization data				X	X				X	X
Adverse event reporting		X	X	X	X		X	X	X	X
BENCHMARK QoC measures (center and patient based)								X		
Patient/physician/coordinator/nursing staff satisfaction			X^d^					X		
Self‐reported working hours per patient (physician, coordinator, nursing staff)								X		

Abbreviations: ECG, electrocardiogram; Echo, echocardiogram; IRB, institutional review board; TAVI, transcatheter aortic valve implantation; QoC, quality of care; TASQ, Toronto Aortic Stenosis Quality of Life Questionnaire; VARC‐2, Valve Academic Research Consortium‐2 consensus document.

^a^
The TAVI and discharge visits of patients being eligible for retrospective documentation must have been documented prior to site's education on BENCHMARK QoC measures. Need for consent form according to local IRB requirements.

^b^
Consent needs to be given prior to the TAVI procedure.

^c^
30 day and 12 months follow‐up (retrospective phase) either hospital visit (preferred) or performed via phone call (no ECG/Echo will be available for this option).

^d^
Optional: Survey could be administered to retrospective patients in combination with consent form (e.g., via postal way).

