### Registry objectives

2.5

The primary objective of the BENCHMARK registry is to document the effect of introducing tailored BENCHMARK QoC measures into TAVI centers to (1) decrease length of hospital stay; and (2) reduce the need for ICU capacity. Secondary objectives will be to streamline diagnostics, minimize staff workload allowing timely delegation of responsibilities, ascertain uncompromised patient safety post‐TAVI (VARC‐2 defined early and time‐related valve safety), improve patient quality of life (QoL), patient and staff satisfaction, and improve the implementation of BENCHMARK QoC measures by each center over time. A full description of the primary and secondary objectives of the BENCHMARK registry is provided in Table 4.

**TABLE 4 clc23711-tbl-0004:** BENCHMARK registry objectives

Primary objectives	
Reduction in length of hospital stay	To reduce the length of hospital stay (door to needle, needle to door, overall stay) in order to reduce overall costs based on hospitalization, and to enable early return to normal life: Separate single hospitalization for diagnostics Door to needle (days) Needle to door (days) Timely discharge to home, rehabilitation center or other institution Economic effect assessment associated with hospitalization changes after implementation of BENCHMARK QoC measures
Reduction of the need for ICU capacity	To accelerate the post‐procedural patient care recovery pathway: Minimize/eliminate time spent in the recovery room, ICU, CCU or IMC and prioritize a rapid return to general ward, in order to reduce the level of invasiveness of post procedural care (e.g., with regard to COVID‐19): Time spent in the recovery room (hours) Time spent on the ICU (hours) Time spent on the CCU (CCU) (hours) Time spent on the IMC (hours/days) Time spent on the general ward (hours/days)

Secondary objectives	
Streamlining of diagnostic and procedural times	To streamline diagnostics to avoid duplication of diagnostic measures and to tighten schedules: Proportion of repeated diagnostic procedures Patient status assessment: physician versus nurse/coordinator To reduce the procedural time without compromising patient safety post TAVI: Time between incision and sheath removal (min) Time between entering and leaving the OR/catheterization laboratory/hybrid room (min)

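### Follow-up mode is tied to phase (visit or phone call at baseline, hospital visit prospectively), so late ECG/Echo-dependent safety outcomes and less serious adverse events may be ascertained unequally in the before-after comparison

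*Protocol article*

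**What the plan says.** Table 2 (section 2.3) gives the follow-up condition for baseline patients as "30 days and 12 month follow‐up: hospital visit or phone call". Footnote c of Table 3 (section 2.4) prefers a hospital visit but allows one "or performed via phone call (no ECG/Echo will be available for this option".

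For the prospective phase, section 2.3 requires that "the patient is scheduled to attend" follow-up at the center 30 days and 12 months after the procedure, and Table 2 adds "both visits taking place in the hospital". Table 3 marks ECG and Echo at both prospective visits, without the phone exception.

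Table 3 schedules VARC-2 safety and efficacy variables, rehospitalization and adverse events at 30 days and 12 months in both phases. Section 2.5 makes it a secondary objective to "ascertain uncompromised patient safety post‐TAVI", specified as VARC-2 early and time-related valve safety. Section 2.2 rests the sample size on the ability to "discriminate any changes in outcomes between the retrospective baseline evaluation phase and the prospective effect documentation phase". The limitations in section 3.2 mention confounding, bias and the lack of central adjudication, but not the difference in follow-up mode.

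**The concern.** The registry is a before-after comparison whose claim is a shorter stay without loss of safety. That claim needs the safety outcomes to be looked for in the same way before and after. Here the way of looking changes at the same point as the care pathway. A valve or conduction finding that needs a test cannot be made over the phone, and a milder event may be reported less completely in a call than at a visit. For the same true rate, the prospective phase could then look less safe, or a real worsening could be put down to better detection. Section 3.2 would not alert a reader to either.

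Separately, the requirement that both visits take place in hospital is an eligibility condition in one phase only. A patient whose follow-up is planned by phone can enter the baseline cohort but not the prospective one. If such patients differ in risk or in length of stay, the two cohorts differ for a reason unrelated to the quality-of-care measures.

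**Working it through.** **1. The plan's own figures.** 30 centers × 30 = 900 baseline patients and 30 × 50 = 1500 prospective patients, total 2400. This reproduces section 2.2. The article gives no event rates, safety margin, error level, power or expected phone share, so the size of any bias cannot be derived. Steps 3 to 5 are illustrations under stated assumptions.

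**2. The two phases side by side (Tables 2 and 3).**

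| | Baseline | Prospective |
|---|---|---|
| Follow-up mode | visit (preferred) or call | hospital visit |
| Mode restricts eligibility | no | yes |
| ECG/Echo at TAVI and discharge | scheduled | scheduled |
| ECG/Echo at 30 days and 12 months | only if a visit took place | scheduled |
| VARC-2 variables and adverse events, late | scheduled | scheduled |

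Table 4 lists, for 30 days and 12 months, mortality, stroke/TIA, major vascular complications, pacemaker (30 days) and readmission, and separately the number and type of adverse events. Conduction disturbance and paravalvular leak stand under device success and procedural complications. The late outcomes most exposed are therefore any ECG/Echo-dependent part of time-related valve safety, and the less serious adverse events. Length of stay and ICU time are settled by discharge, so follow-up mode cannot affect how they are detected.

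**3. Missing tests.** Let f be the share of baseline patients followed by phone (assumed). At most 900 × (1 − f) baseline patients have a follow-up ECG/Echo: 900, 675, 450, 225 or 0 for f = 0, 25, 50, 75 or 100%. What this does to a rate depends on the denominator. Take f = 50% and a true rate of 6% in both phases:
- expected findings among the 450 examined: 0.06 × 450 = 27;
- untested patients counted as event-free: 27/900 = 3%, half the prospective rate;
- untested patients treated as missing: 27/450 = 6%, no bias unless attendance is related to outcome.

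**4. Events reported less completely by phone.** Let p be the true rate (equal in both phases) and s the share of events a call detects relative to a visit. The observed baseline rate is p × (1 − f + f × s). With p = 10% and n = 900 against 1500, the last column is the chance that a two-sided 5% test shows a significant prospective excess:

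| f | s | Baseline observed | Spurious excess | Chance of significance |
|---|---|---|---|---|
| 25% | 80% | 9.5% | 0.5 points | 6% |
| 25% | 50% | 8.75% | 1.25 points | 17% |
| 50% | 80% | 9.0% | 1.0 point | 12% |
| 50% | 50% | 7.5% | 2.5 points | 54% |
| 75% | 80% | 8.5% | 1.5 points | 23% |
| 75% | 50% | 6.25% | 3.75 points | 90% |

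If s = 100%, which is plausible for death, the bias is zero at every f.

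**5. Selection through the in-hospital condition.** Suppose a share g of patients is lost prospectively and carries r times the risk of the rest, with an overall rate of 10%. The prospective rate is then 10% / (1 − g + g × r). For g = 5%, r = 2 this is 10%/1.05 = 9.5%; for g = 20%, r = 3 it is 10%/1.40 = 7.1%; for r = 1 it stays at 10%. For stay, if 5% are lost and they stay 4 days longer than the average patient, the mean falls by about 0.05 × 4 = 0.2 days. With an assumed SD of 5 days the standard error of the difference is 5 × √(1/900 + 1/1500) = 0.21 days. All of g, r, 4 days and SD 5 are assumptions.

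**The case against.** The strongest reply is that most late endpoints in Table 4 need no ECG or Echo, and that the valve and conduction items sit in the procedural group, where both phases schedule the tests. On this view the plan already compares mostly what either mode can establish. That largely stands, and it narrows the point. It does not remove it, because section 2.5 names time-related valve safety and Table 4 includes the number and type of adverse events. What valve safety requires beyond Table 4 is not spelled out in the article.

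A reader might infer that test-dependent rates will look doubled in the prospective phase. The documents do not support that. Footnote c makes the tests unavailable, that is missing, and nothing says missing tests count as negative.

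A reader might also infer that fitter patients are selected prospectively. The documents do not say so. The criterion is being scheduled to attend, enrolment is consecutive in both phases, and no fitness or travel requirement appears. Other differences could act the other way: only the baseline phase excludes largely incomplete data, and its consent may be sought after the event, which could favor survivors where no waiver applies.

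It can further be said that EuroSCORE II, comorbidities and frailty are collected in both phases, so a shift in case mix can be examined, and that section 3.2 already admits confounding. Both are true. Neither equalizes ascertainment at follow-up. Finally, a call is a practical option for a retrospective cohort, and visits are preferred, so the actual phone share may be small.

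**Conclusion.** The point holds in a limited form. By the eligibility criteria and the schedule, follow-up mode differs between the two phases being compared, and the limitations do not name this. Late ECG/Echo-dependent valve-safety outcomes and less serious adverse events may be ascertained unequally. Under the assumed ranges the spurious prospective excess runs from zero, through 0.5 points, to 3.75 points on a 10% rate; for test-dependent findings it turns on how missing tests are handled. Death, stroke, pacemaker and readmission are much less exposed.

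The in-hospital condition may also select patients. That is the only route by which the primary outcomes could be touched, its net direction is unknown, and the illustrated effect on stay is about one standard error. It would go too far to say that safety as a whole is measured differently or that the primary comparison is biased. The matter should still be corrected, because the correction is cheap and the safety claim is central to the registry's purpose.

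**What to change.** - Use the same eligibility wording in both phases, "hospital visit or phone call" with the visit preferred, so that planned mode of follow-up decides nobody's inclusion.
- Record the mode of each 30-day and 12-month contact in the eCRF in both phases, and report the phone share by phase.
- Limit the between-phase comparison at 30 days and 12 months to events either mode can establish: death, stroke, pacemaker and readmission.
- Compare ECG/Echo-dependent outcomes between phases at discharge, where Table 3 schedules the tests in both, and note that earlier discharge in the prospective phase shortens that window.
- Report later ECG/Echo findings descriptively, with the number examined as the denominator, and name the difference in follow-up mode among the limitations.

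The cost is one changed criterion, one eCRF field and some analysis wording. The downside is that some prospective patients will lack late ECG/Echo.
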